### Relevant concomitant care permitted or prohibited during the trial {11d}

Perioperative use of medications that substantially affect cognition (e.g., benzodiazepine sleep aids, anticholinergic antiemetics/antihistamines, and high-dose antipsychotics for non-delirium indications) will be prohibited unless clinically indispensable and the expected benefits outweigh the risks to study validity. The anesthesia and surgical teams will follow a standardized, enhanced recovery after surgery (ERAS)-consistent pathway to minimize such exposure; where antiemetic or sedative and analgesic therapy is required, non-anticholinergic alternatives (e.g., ondansetron) and opioid-sparing strategies will be preferred; meperidine (pethidine) will be avoided. Any rescue use of prohibited/limited agents will be prospectively recorded (drug, dose, frequency, duration, timing, indication) as a protocol deviation without excluding the participant from intention-to-treat analyses. Medication exposure will be captured during hospitalization and at discharge. Quantitative exposure metrics—including total opioid burden expressed as morphine milligram equivalents (MME) and a composite psychotropic medication score—will be incorporated as covariates in the primary regression models to adjust for potential confounding. A prespecified sensitivity analysis will exclude participants with extreme exposure to potentially confounding medications to assess robustness.

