### Recruitment {15}

Recruitment will take place at Shanghai Fourth People’s Hospital during the elective TKA pathway. Potential participants will be pre-screened at the pre-assessment clinic and on the orthopedic ward against the eligibility criteria (e.g., radiographic severity consistent with Kellgren–Lawrence grade ≥ 3), with written informed consent obtained prior to allocation. Recruitment strategies include surgeon referral at pre-assessment clinics, ward-based screening, and patient-facing materials (posters and flyers). Accrual numbers will be reported only under Trial status; detailed inclusion/exclusion criteria are provided in the “Eligibility criteria {10}” section.

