### Methods in analysis to handle protocol non-adherence and any statistical methods to handle missing data {20c}

Analyses will follow the intention-to-treat principle, retaining all randomized participants in their allocated groups. To minimize loss to follow-up, we will employ proactive retention strategies (appointment reminders, flexible assessment windows, and phone/text follow-ups). For the primary endpoint and other repeated continuous outcomes, linear mixed-effects models will be estimated under a missing-at-random assumption using maximum likelihood; results will be stress-tested by prespecified sensitivity analyses including multiple imputation (*m* = 20) and a conservative worst-case scenario. Participants who deviate from the intervention protocol will remain in the ITT analysis; per-protocol/sensitivity analyses may be reported descriptively. We will not replace randomized participants; if attrition exceeds the prespecified allowance and materially threatens power, the TSC may, on DSMB advice and blinded aggregate information, approve extending recruitment to preserve target precision.

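### The concomitant-drug sensitivity analysis excludes randomised participants on exposure arising largely after allocation, so its agreement or disagreement with the ITT result is not reliable evidence of robustness

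*Protocol article*

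**What the plan says.** All statements are in the protocol article.

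- Section {11d}, on concomitant care, announces the analysis: "A prespecified sensitivity analysis will exclude participants with extreme exposure to potentially confounding medications to assess robustness".
- The same section says when exposure is recorded: "Medication exposure will be captured during hospitalization and at discharge". It names the metrics: "including total opioid burden expressed as morphine milligram equivalents (MME) and a composite psychotropic medication score".
- Rescue use of a prohibited or limited agent is logged with its timing and indication, and is treated "as a protocol deviation without excluding the participant from intention-to-treat analyses".
- The list of prohibited drugs names antipsychotics only in this form: "high-dose antipsychotics for non-delirium indications".
- Section {15} places allocation after consent: "with written informed consent obtained prior to allocation". Section {11a} places all five rTMS or sham sessions before surgery.
- Section {12} sets the primary outcome as POCD at postoperative day seven, derived from MoCA items and compared as a risk ratio.
- Section {20c} commits to intention-to-treat, "retaining all randomized participants in their allocated groups".

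**The concern.** A sensitivity analysis should vary an assumption and leave the randomised comparison intact. This one changes who is compared, using a variable that arises largely after allocation.

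Two routes link that variable to the result. First, worsening cognition can lead to psychotropic drugs. By prohibiting high-dose antipsychotics only outside delirium, section {11d} leaves room for their use in delirium, and the key to Table 1 lists a confusion assessment. Second, section {6a} hypothesises that rTMS improves early postoperative cognition. If it does, the arm can change drug exposure through the endpoint itself.

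Exposure is captured up to discharge with no stated end at the day-seven assessment, so some of it may even follow the outcome.

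What is at stake is how the check is read. It could make a real effect look weaker or stronger than it is, or show a difference where there is none. Either might be reported as information about robustness.

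**Working it through.** **Inputs from the article.** POCD is assumed at 40%, with a 15-point reduction (section {14}), so 40% vs 25%. The true risk ratio is 0.25/0.40 = 0.625 and the odds ratio is (0.25/0.75)/(0.40/0.60) = 0.50. Evaluable participants per arm are 186/3 = 62. The article gives no figure for the sensitivity analysis, so there is none to reproduce.

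**Assumed inputs.** The article gives no exposure rates. I take 5% of non-cases as extreme users (e0 = 0.05) and 10–40% of POCD cases (e1), equal or unequal between arms.

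**Formula.** POCD rate among those kept = p(1−e1) / [p(1−e1) + (1−p)(1−e0)].

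- p = 0.40: e1 = 0.10 gives 0.36/0.93 = 38.7%; e1 = 0.20 gives 0.32/0.89 = 36.0%; e1 = 0.40 gives 0.24/0.81 = 29.6%.
- p = 0.25: e1 = 0.10 gives 0.225/0.9375 = 24.0%; e1 = 0.20 gives 0.20/0.9125 = 21.9%; e1 = 0.40 gives 0.15/0.8625 = 17.4%.

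In head counts, the sham arm has 0.40 × 62 ≈ 25 cases and 37 non-cases. With e1 of 0.20–0.40, 5 to 10 cases and about 2 non-cases are dropped.

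**Results**

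| True rates, sham / active | e1, sham / active | Rates after exclusion | Difference (points) | RR | OR |
|---|---|---|---|---|---|
| 40 / 25 | no exclusion | 40.0 / 25.0 | 15.0 | 0.625 | 0.50 |
| 40 / 25 | 0.20 / 0.20 | 36.0 / 21.9 | 14.0 | 0.61 | 0.50 |
| 40 / 25 | 0.40 / 0.40 | 29.6 / 17.4 | 12.2 | 0.59 | 0.50 |
| 40 / 25 | 0.20 / 0.10 | 36.0 / 24.0 | 12.0 | 0.67 | 0.56 |
| 40 / 25 | 0.40 / 0.20 | 29.6 / 21.9 | 7.7 | 0.74 | 0.67 |
| 40 / 25 | 0.10 / 0.20 | 38.7 / 21.9 | 16.8 | 0.57 | 0.44 |
| 40 / 25 | 0.20 / 0.40 | 36.0 / 17.4 | 18.6 | 0.48 | 0.375 |
| 40 / 40 | equal | equal | 0 | 1.00 | 1.00 |
| 40 / 40 | 0.20 / 0.10 | 36.0 / 38.7 | −2.8 | 1.08 | 1.13 |
| 40 / 40 | 0.40 / 0.20 | 29.6 / 36.0 | −6.3 | 1.21 | 1.33 |
| 40 / 40 | 0.10 / 0.20 | 38.7 / 36.0 | 2.8 | 0.93 | 0.89 |
| 40 / 40 | 0.20 / 0.40 | 36.0 / 29.6 | 6.3 | 0.82 | 0.75 |

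**What drives the shift.** Exclusion multiplies the odds ratio by [(1−e1)/(1−e0)] in the active arm divided by the same quantity in the sham arm. Equal exclusion gives a factor of 1. Exclusion that differs by arm but is unrelated to POCD also gives 1: dropping 20% of sham and 10% of active participants regardless of POCD leaves the RR at 0.625. Material distortion needs exclusion that depends on POCD to a different degree in each arm.

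**The case against.** The strongest reply is that the mechanism is possible but not shown. No section says that POCD drives drug use. POCD here is a blinded, test-based decline in MoCA items, not a diagnosis that prompts prescribing. Opioid burden may mainly reflect pain and surgery. The antipsychotic wording takes delirium use out of the prohibited class, and delirium is not the endpoint. All of this stands. A reader might infer that the analysis does remove POCD cases selectively; the article supports only that it can.

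The larger shifts are also open to challenge. With 40% of cases and 5% of non-cases extreme, 0.40 × 0.40 + 0.60 × 0.05 = 19% of the sham arm is dropped, which is high for a pathway meant to limit such drugs. The values 0.74, 1.21 and 0.82 all depend on that rate. With 20% as the higher rate, the range is narrower: 0.67 under the assumed effect when rTMS lowers exposure, and 0.93–1.08 under no effect.

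Three further inferences are not supported.

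- *This is the only check on drug use.* It is not. The preceding sentence of {11d} says the exposure metrics "will be incorporated as covariates in the primary regression models to adjust for potential confounding". That has its own difficulty and is a separate issue.
- *The excluded group can be picked after seeing the data, because extreme has no cut-off.* A numeric threshold may stand in a statistical analysis plan that is not shown, and section {17a} keeps the statisticians blinded.
- *The check carries no information at all.* It is supportive, stands beside a retained ITT analysis, and could be informative if exposure were limited to a window before the outcome and not driven by it.

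The reply does not remove the core point. The article commits to excluding randomised participants on largely post-allocation exposure, with no stated limit to exposure before the outcome.

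**Conclusion.** The point holds as a caution about one supportive analysis that should be acted on. Because the exclusion uses exposure that the cognitive state and the arm can both affect, the participants who remain are no longer the randomised groups. Neither agreement nor disagreement with the ITT result can be relied on as evidence of robustness.

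The size rests wholly on assumed exposure rates. Selective loss of cases that is equal across arms is a minor matter: the odds ratio and the null are untouched, and the RR moves slightly away from 1. Arm-dependent loss is what matters. It takes the RR to about 0.67–0.74 if rTMS halves extreme exposure among cases, and lower than 0.625 if the imbalance runs the other way. With no effect it gives 0.82–1.21.

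A reader might infer that the trial's main result is compromised. It is not on this ground: sections {11d}, {20a} and {20c} keep ITT as the main analysis.

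**What to change.** Replace the exclusion in section {11d} with a sensitivity analysis that keeps all randomised participants in their allocated arms. One workable form counts as POCD anyone who received a prohibited or limited agent after allocation and before the day-seven MoCA. This is a composite outcome and should be labelled so. The timing of rescue use is already recorded, so no new data are needed.

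That form does not cover ordinary opioid use, because opioids are not listed as prohibited. Opioid MME and the psychotropic score should therefore be reported by arm descriptively.

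If a restricted analysis is kept, restrict only on drug use recorded before allocation. If outcomes of drug users are imputed, label the result as answering a hypothetical question under an untestable missing-at-random assumption. It sets observed outcomes aside and partly shares the weakness of the exclusion, so it should not be the main replacement.

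The cost is a change of wording, a little programming, and a sensitivity result that may be less favourable or wider.

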### Provisions for post-trial care {30}

Waiting for the end of the experiment, the control group will receive 5 rTMS treatments free of charge. If other symptoms of the subjects worsen during the study, rTMS treatment should be stopped immediately and symptomatic treatment should be provided free of charge, as well as psychological counseling for the patients. If the injury is serious, the relevant specialists will be invited to treat the injury and compensate for the medical expenses.

### Outcomes {12}

#### Primary outcome (five-element specification)

Domain: POCD.

Specific measurement: MoCA administered at four scheduled assessments (preoperative day six, preoperative day one (baseline), postoperative day three, postoperative day seven) by a trained, blinded assessor.

Metric: Binary classification of POCD at each postoperative assessment. POCD is defined a priori as a ≥ 20% decline from baseline in ≥ 2 MoCA items (Newman criteria) [17].

Method of aggregation: The group-level proportion with POCD at postoperative day seven (primary time point); between-group effect expressed as risk ratio with 95% CI from a log-binomial model (logistic regression if non-convergent), adjusted for age, sex, education, and baseline MoCA.

Time point: postoperative day seven (primary); postoperative day three analyzed as supportive.

#### Secondary outcomes (five-element specification)

MoCA total score—measurement: total score (0–30); metric: change from baseline; aggregation: mean (SD) and mean difference (95% CI) from linear mixed models; time points: preoperative day six, preoperative day one, postoperative day three, postoperative day seven.

Digit Span Test (DST) (forward/backward)—measurement per standard DST; metric: value and change; aggregation: mean (SD) and mean difference; time points: preoperative day six, preoperative day one, postoperative day three, postoperative day seven.

Digit Symbol Substitution Test (DSST)—measurement: number correct in 90 s; metric: value and change; aggregation: mean (SD) and mean difference; time points: preoperative day six, preoperative day one, postoperative day three, postoperative day seven.

Trail Making Test (TMT)—measurement: time to completion (s); metric: value and change; aggregation: mean (SD); if skewed, median (IQR) and Hodges–Lehmann difference (pre-specified); time points: preoperative day six, preoperative day one, postoperative day three, postoperative day seven.

Delayed Story Recall (DSR)—measurement: story recall points; metric: value and change; aggregation: mean (SD) and mean difference; time points: preoperative day six, preoperative day one, postoperative day three, postoperative day seven.

Inflammatory markers (IL-1β, IL-6, TNF-α, HMGB1)—measurement: serum ELISA (pg/mL); metric: log-change from baseline; aggregation: geometric mean ratio (ANCOVA, baseline-adjusted) (or mean difference if normal); time points: preoperative day six, preoperative day one, postoperative day three, postoperative day seven.

All time points conform to the pre-specified SPIRIT schedule (preoperative day six, preoperative day one, postoperative day three, postoperative day seven); statistical baseline is defined as pre-op day 1 for all change analyses.

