#### Active rTMS group

The active rTMS group will be given active rTMS treatment based on standardized perioperative management. Active rTMS will be delivered using a magnetic stimulator (YRD-CCY-1, YIRUIDE Medical Equipment, Wuhan, China) with a figure-of-eight 70-mm coil positioned tangential to the scalp over the left dorsolateral prefrontal cortex (DLPFC; 10–20 system F3). Stimulation will be applied at 10 Hz in 5-s trains with 25-s inter-train intervals, 2000 pulses per session, at an intensity of 100% of the resting motor threshold (RMT). RMT will be defined as the lowest stimulator output that elicits motor-evoked potentials (MEPs) ≥ 50 μV in the relaxed right abductor pollicis brevis in ≥ 5 of 10 trials. Sessions will be delivered once daily for five consecutive pre-operative days. No post-operative rTMS will be delivered in this protocol; surgery is scheduled within 24–48 h after the final pre-operative session. Participants will be continuously monitored; if intolerable local discomfort occurs, stimulation will be stopped immediately and documented.

Rationale for stimulation site: The left dorsolateral prefrontal cortex (DLPFC) is a hub of executive-control and working-memory networks implicated in early postoperative cognition. Against the peri-operative neuroinflammatory background relevant to POCD (e.g., IL-1β, IL-6, TNF-α, HMGB1), prefrontal neuromodulation offers a biologically plausible route to support cognition and modulate inflammatory signaling. Accordingly, the left DLPFC (F3) was selected as the stimulation target.

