### Participant timeline {13}

Following enrollment, each outcome indicator will be assessed at four time points: before the rTMS intervention (on preoperative day six), after the completion of the rTMS intervention (on preoperative day one), on postoperative day three, and on postoperative day seven. The schedule of enrollment, interventions, and assessments is summarized in the Standard Protocol Items: Recommendations for Interventional Trials (SPIRIT) figure.

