### Statistical methods

#### Statistical methods for primary and secondary outcomes {20a}

Analyses will follow intention-to-treat. Primary endpoint (POCD at postoperative day seven) will be compared between groups using log-binomial regression to estimate risk ratios (95% CI), adjusted for age, sex, education, and baseline MoCA; logistic regression will be used if convergence issues arise. A supportive analysis will model POCD trajectories at postoperative day three and postoperative day seven using generalized estimating equations with a log link.

Continuous secondary outcomes (MoCA total, DST, DSST, TMT, DSR) will be analyzed using linear mixed-effects models (fixed effects for group, time, and group × time; random intercept for participant), adjusting for baseline. For TMT, if residuals are markedly non-normal, we will report median (IQR) and between-group Hodges–Lehmann differences as pre-specified sensitivity analyses. Inflammatory markers will be log-transformed and analyzed using ANCOVA at each post-op time point with baseline adjustment; results will be back-transformed as geometric mean ratios (95% CI). Missing data will be handled under a missing-at-random assumption via maximum likelihood; multiple imputation (*m* = 20) will be a sensitivity analysis. Multiplicity across secondary outcomes will be controlled by the Benjamini–Hochberg procedure (false discovery rate 5%).

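### The baseline is set at preoperative day one, after all five rTMS sessions, so POCD, change scores and baseline-adjusted models start from a treated value and can hide or reverse the effect

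*Protocol article*

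**What the plan says.** Participant timeline {13} of the protocol article lists four assessments of every outcome. The first is "before the rTMS intervention (on preoperative day six"; the second is "after the completion of the rTMS intervention (on preoperative day one"; the others are on postoperative days three and seven. The Active rTMS group section gives the schedule: "Sessions will be delivered once daily for five consecutive pre-operative days", and "No post-operative rTMS will be delivered in this protocol".

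The baseline is nevertheless the second visit. The primary outcome specification labels it "preoperative day one (baseline" and defines POCD as a 20% or greater "decline from baseline in" at least two MoCA items. The secondary outcomes section closes with the general rule that "statistical baseline is defined as pre-op day 1 for all change analyses".

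Statistical methods {20a} then uses baseline as a covariate. The primary log-binomial model includes baseline MoCA, the mixed models for the cognitive tests adjust for baseline, and "Inflammatory markers will be log-transformed and analyzed using ANCOVA at each post-op time point with baseline adjustment". The protocol gives no reason for choosing the later preoperative visit.

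**The concern.** Day one falls after randomisation and after the whole treatment course. Any effect of rTMS before surgery is already in the day-one value, so subtracting it or adjusting for it removes part of what the trial sets out to measure. Objectives {7} asks about the effect of perioperative rTMS on postoperative cognitive function, and the hypothesis in {6a} is better early postoperative cognition and smaller marker rises than under sham or standard care.

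The Discussion describes the regimen as pre-conditioning, which supposes that stimulation changes something before surgery. If it raises cognition, treated patients have further to fall and are classed as POCD more often at the same postoperative performance. If it lowers cytokines before surgery, ANCOVA on day one removes that part of the benefit. The primary endpoint and all baseline-referenced secondary analyses are affected.

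There is also a smaller fault. The MoCA total score is to be analysed as change from baseline, and preoperative day one is among its listed time points. Change there is zero for every patient by construction.

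**Working it through.** The plan has no figure of its own for this bias. The only yardstick is the effect in Sample size {14}: POCD falling from 40% by 15 points. All other inputs below are assumptions.

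**1. Algebra.** Let g be the active-minus-sham difference at preoperative day one, e the difference at postoperative day seven, and b the within-arm slope of day seven on day one. Randomisation makes the expected difference at day six zero.

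- Change from day six: e − 0 = e. Change from day one: e − g.
- ANCOVA on day six: e. ANCOVA on day one: e − b·g.

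With g = 1 point and b = 0.6 or 0.8:

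| True e | Change or ANCOVA, day six | Change, day one | ANCOVA, day one, b = 0.6 | ANCOVA, day one, b = 0.8 |
|---|---|---|---|---|
| 1.0 | 1.0 | 0.0 | 0.4 | 0.2 |
| 0.5 | 0.5 | −0.5 | −0.1 | −0.3 |
| 0.0 | 0.0 | −1.0 | −0.6 | −0.8 |

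A simulation of 200,000 patients per setting agreed to within about 0.01. With g = 0 and e = 1, all methods returned 1.0.

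**2. Inflammatory markers (SD units).** Assume a direct postoperative effect d = −0.10, a preoperative effect g of −0.10 to −0.20, and b of 0.4 to 0.8. The total effect is e = d + b·g.

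- Smallest: −0.10 + 0.4 × (−0.10) = −0.14.
- Largest: −0.10 + 0.8 × (−0.20) = −0.26.
- ANCOVA on day one: e − b·g = d = −0.10 throughout.

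The share lost is 0.04/0.14 = 29% to 0.16/0.26 = 62%.

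**3. The POCD rule.** Two simulations with different assumed structures were used.

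*Thirteen items, 30 points, entry score at least 26, assumed item difficulties, 300,000 patients per setting.* The shift was applied at day one only, so postoperative scores were the same in both arms. A gain of 0.3 to 0.9 MoCA points raised apparent POCD in the active arm by 3 to 8 percentage points from day one and by about 0 from day six.

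*Seven domains, a fall of at least 20% in at least two.* Assumed retest SD 10%, mean surgical decline 8%, between-patient SD of decline 10%. The untreated POCD rate was 42%.

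| Effect of rTMS | POCD, day-six baseline | POCD, day-one baseline |
|---|---|---|
| None | 42% | 42% |
| 5% gain, fully kept at day seven | 27% | 39% |
| 5% gain, 2.5% kept | 34% | 47% |
| 5% gain, fully lost | 42% | 56% |
| No gain at day one, 5% benefit at day seven | 27% | 27% |

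With retest SD from 8% to 12% and mean decline of 4% or 8%, the fully kept gain was worth 11 to 15 points from day six but only about 3 from day one. The partly kept gain was a reduction of 6 to 8 points from day six and an increase of 4 to 5 points from day one.

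**4. Zero-change rows.** This applies only if day-one change values enter the mixed model as responses. If one of four rows per patient is identically zero, the pooled variance shrinks by a factor of 0.75 and the standard error by √0.75 = 0.866. The nominal critical value of 1.96 then acts as 1.96 × 0.866 = 1.70, a two-sided type I error of 0.09. Simulation gave 0.080 to 0.098 with the zero rows and 0.05 with postoperative rows only.

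**The case against.** The best defence is that a value taken just before surgery is the natural reference for decline across surgery. The text gives some support: the hypothesis speaks of attenuating perioperative marker increases, and {21b} calls the endpoint a short-term change in cognitive performance. Unadjusted, decline from day one is still a comparison of randomised arms and is not biased by this choice if rTMS does nothing. That is right as far as it goes. But the protocol never states decline across surgery as its target, and the same hypothesis claims better postoperative cognition, which this reference cannot isolate. Nor does that reading justify adjusting for a post-treatment covariate.

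The magnitudes are illustrations. The two POCD models disagree on size (3 to 8 points against about 14 for a gain fully lost), and the entry rule of MoCA 26 or more leaves at most 4 points of headroom. This stands for the MoCA, but it does not limit shifts in the markers, the Digit Symbol test or Trail Making.

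The zero-row point is narrow. The other tests are specified as value and change, the marker ANCOVA is confined to postoperative visits, and the list of visits may be only an assessment schedule. The type I error figure is therefore conditional.

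Finally, if the day-six MoCA also serves as the eligibility score, which the protocol does not say, regression to the mean would raise POCD measured from day six. An item-level simulation with assumed difficulties put this at about 1 to 3 points in the control arm. It is equal across arms in expectation and does not create a spurious difference between them.

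**Conclusion.** The concern holds and should be fixed before the analysis. The timing is explicit and consistent across {11a}, {12} and {13}: day one follows the full treatment course and is still used as the baseline. As written, the plan does not estimate the total effect of rTMS on postoperative cognition or markers.

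The form of the bias, g for change scores and b·g for ANCOVA, follows from the design. Its size does not, because the protocol gives no expected day-one effect, slope or retest variability. Under the assumptions shown, the distortion of POCD ranges from a few points to more than ten, against a planned effect of 15, and a partly lasting benefit can appear as harm. If rTMS leaves day-one values unchanged, this bias is absent.

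**What to change.** In {12} and {20a}, define baseline as preoperative day six for the POCD classification, the MoCA covariate, all change scores, the mixed-model adjustment and the marker ANCOVA. Report preoperative day one as an on-treatment outcome. State that only visits after baseline enter the mixed models as responses. Keep POCD measured from day one as a sensitivity analysis, described as decline across surgery.

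No new data are needed, because every outcome is already measured on day six. The longer interval from baseline to outcome may add some practice effect, which should be equal across arms. Enrolment began in March 2024, so a changed reference for the primary endpoint is a substantial amendment, with the ethics notification and registry update described in {25}. It should be made, dated and justified before anyone sees outcome data by arm.
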